## Abstract

**Background:**

Cellulitis is a painful, potentially serious, infectious process of the dermal and subdermal tissues and represents a significant disease burden. The statistical analysis plan (SAP) for the Penicillin for the Emergency Department Outpatient treatment of CELLulitis (PEDOCELL) trial is described here. The PEDOCELL trial is a multicentre, randomised, parallel-arm, double-blinded, non-inferiority clinical trial comparing the efficacy of flucloxacillin (monotherapy) with combination flucloxacillin/phenoxymethylpenicillin (dual therapy) for the outpatient treatment of cellulitis in the emergency department (ED) setting. To prevent outcome reporting bias, selective reporting and data-driven results, the a priori-defined, detailed SAP is presented here.

**Methods/design:**

Patients will be randomised to either orally administered flucloxacillin 500 mg four times daily and placebo or orally administered 500 mg of flucloxacillin four times daily and phenoxymethylpenicillin 500 mg four times daily. The trial consists of a 7-day intervention period and a 2-week follow-up period. Study measurements will be taken at four specific time points: at patient enrolment, day 2–3 after enrolment and commencing treatment (early clinical response (ECR) visit), day 8–10 after enrolment (end-of-treatment (EOT) visit) and day 14–21 after enrolment (test-of-cure (TOC) visit). The primary outcome measure is investigator-determined clinical response measured at the TOC visit. The secondary outcomes are as follows: lesion size at ECR, clinical treatment failure at each follow-up visit, adherence and persistence of trial patients with orally administered antibiotic therapy at EOT, health-related quality of life (HRQoL) and pharmacoeconomic assessments. The plan for the presentation and comparison of baseline characteristics and outcomes is described in this paper.

**Discussion:**

This trial aims to establish the non-inferiority of orally administered flucloxacillin monotherapy with orally administered flucloxacillin/phenoxymethylpenicillin dual therapy for the ED-directed outpatient treatment of cellulitis. In doing so, this trial will bridge a knowledge gap in this understudied and common condition and will be relevant to clinicians across several different disciplines. The SAP for the PEDOCELL trial was developed a priori in order to minimise analysis bias.

**Trial registration:**

EU Clinical Trials Register (EudraCT number: 2016-001528-69). Registered on 5 April 2016.

ClinicalTrials.gov, ID: NCT02922686. Registered on 9 August 2016.

**Electronic supplementary material:**

The online version of this article (doi:10.1186/s13063-017-2121-2) contains supplementary material, which is available to authorized users.

## Introduction

The Penicillin for the Emergency Department Outpatient treatment of CELLulitis (PEDOCELL) trial is a multicentre, randomised, parallel-arm, double-blinded, non-inferiority clinical trial comparing the efficacy of orally administered flucloxacillin monotherapy with combination orally administered flucloxacillin/phenoxymethylpenicillin for the outpatient treatment of cellulitis in the emergency department (ED) setting.

To prevent outcome reporting bias and data-driven analysis results, the International Conference on Harmonisation of Good Clinical Practice and others have recommended that clinical trials should be analysed according to a pre-specified statistical analysis plan (SAP) [1]. In this paper the SAP that has been finalised prior to any recruitment, and to which all data analyses in the main publication of the trial results will adhere, is described. The PEDOCELL trial has been registered with ClinicalTrials.gov (NCT02922686) and EU Clinical Trials Register (EudraCT number: 2016-001528-69). The SAP was written and submitted without knowledge of the outcome data.

In 2013, the protocol for a randomised controlled trial (RCT) describing a similar intervention (flucloxacillin and phenoxymethylpenicillin versus flucloxacillin and placebo) was published by members of this research group [2]. However, in 2010 and again in 2013, the United States (US) Food and Drug Administration (FDA) recommended a different primary outcome measure for trials of antibiotic treatment for acute bacterial skin and skin structure infections (ABSSSI), which directly impacted on the proposed primary and secondary outcome measures to be utilized in the previous version of this study. In addition, the investigators developed several secondary outcome measures including validation of the Extremity Soft Tissue Infection (ESTI) score, measurement of health-related quality of life (HRQoL) using the EuroQol – 5 dimensions – 5 levels (EQ-5D-5L) instrument, a pharmacoeconomic analysis to assess cost per quality-adjusted life year (QALY) of the new treatment, and an adherence substudy using an electronic medication event monitoring system (MEMS® cap). The investigators have also the created a credible Data and Safety Monitoring Committee (DSMC), a scientific advisory group, the nomination of five site investigators and the recruitment of two full-time research nurses to join the project team. Given the scope and scale of these changes, it was decided that the submission of an entirely new application to the relevant authorities was required. An overview of the current study design is outlined below.

## Trial overview

The PEDOCELL trial is a multicentre, randomised, parallel-arm, non-inferiority trial which will be conducted in five hospitals in the Republic of Ireland (Beaumont Hospital, Connolly Hospital, Cork University Hospital, Mater Misericordiae University Hospital and Mercy University Hospital). It may be necessary to include two contingency sites, dependent on recruitment rates. Those sites are Our Lady of Lourdes Hospital in Drogheda and Midlands Regional Hospital in Tullamore. The trial consists of a 7-day intervention period and a 2-week follow-up period.

Measurements will be undertaken at four specific time points: at the baseline visit, at the early clinical response (ECR) visit on day 2–3 after enrolment, at the end-of-treatment (EOT) visit on day 8–10 post enrolment and at the test-of-cure (TOC) visit on day 14–21 post enrolment.

The study design also includes a substudy to evaluate patient adherence and persistence with therapy using an electronic MEMS® cap. The purpose of this substudy is to describe these parameters in the understudied area of short-course outpatient antibiotic treatment as well as to provide evidence for any adjustments in analysis based on medication-taking behaviour.

## Objectives

The primary objective of the PEDOCELL trial is to conduct a multicentre, randomised, parallel-arm, non-inferiority trial and to determine if orally administered flucloxacillin alone (monotherapy) is non-inferior to orally administered flucloxacillin and phenoxymethylpenicillin (dual therapy) for the ED-directed outpatient treatment of cellulitis.

The secondary objectives of the PEDOCELL trial are:To investigate the relationship between reduction in lesion surface area measured at the ECR visit, and investigator-determined clinical cure measured at the TOC visit. A reduction of ≥ 20% of lesion surface area is the most recently recommended primary outcome measure by the US FDA, while clinical cure is recommended by the European Medicines Agency (EMA)To measure and investigate adherence and persistence of trial patients with outpatient antibiotic therapy measured by self-report and by counting the number of unused study medications at the EOT visit. In addition, to describe adherence and persistence in a substudy using an electronic MEMS**®** capTo perform a within-trial evaluation of the cost per QALY gained from the use of orally administered flucloxacillin compared with combination therapy over a 1-month time horizon from the perspective of the health care payer (direct costs). In a secondary analysis the perspective will be extended to consider costs related to the intervention falling on the patient and the governmentTo externally validate the ESTI score, a HRQoL questionnaire designed to quantify the impact of cellulitis and other ABSSSI on patient HRQoL in clinical trials. Although investigator-determined clinical cure could be considered a composite of objective signs of cure and subjective patient experiences, the ESTI score will allow for quantification of these experiences and the effects of treatment

## Trial procedure

Consecutive patients attending the participating EDs with cellulitis, who meet the inclusion criteria and none of the exclusion criteria for the trial, will be considered eligible for enrolment. Eligibility for enrolment will be determined by a suitably trained member of the research team.

### Inclusion criteria

Clinically diagnosed cellulitis, affecting any body part, excluding the perineum, and having any two of the following signs:ErythemaWarmthTenderness/pain of the affected areaOedema/indurationRegional lymphadenopathy
Cellulitis deemed treatable with orally administered outpatient antibiotics in which either combination of antibiotic is likely to produce a clinical response (Eron Class 1–2)Written informed consent obtainedSixteen years of age or olderFluency in written and spoken EnglishWilling to return for study follow-up or to have the research nurse visit them for follow-upWilling to receive a telephone call from a study investigator

### Exclusion criteria

Penicillin allergy (self-reported or confirmed)Any cellulitis that treating clinicians deem treatable with intravenously administered antibioticsAny cellulitis of the perineal regionPatients who have received more than 24 h of effective antibiotics for the current episode of acute cellulitisAny medical condition, based on clinical judgment, that may interfere with interpretation of the primary outcome measures (e.g. chronic skin condition at the cellulitis lesion site)Immunodeficiency from primary or secondary causes (e.g. corticosteroids, chemotherapeutic agents)Previous history of renal dysfunction or known chronic kidney disease under the care of a nephrologistPrevious history of liver dysfunction (defined as chronically deranged liver function tests elicited from medical notes or history)Suspected or confirmed septic arthritisSuspected or confirmed osteomyelitisInfection involving prosthetic materialPregnant or lactating womenPatients with a previous history of flucloxacillin-associated jaundice/hepatic dysfunctionPatients with a previous history of methicillin-resistant *Staphylococcus aureus* (MRSA) colonisation/infectionPatients with lactose intolerance diagnosed by a medical professional

### Interventions

Patients will be randomised in a blinded fashion to either orally administered flucloxacillin 500 mg and placebo, or orally administered flucloxacillin 500 mg and phenoxymethylpenicillin 500 mg, both four times daily for 7 days.

### Determination of sample size

The sample size per trial arm was calculated based on an assumed treatment success rate of 85% with orally administered flucloxacillin and phenoxymethylpenicillin, a non-inferiority threshold *Δ* = 12.5% and *α* = 0.025 (as this is a non-inferiority study). Sample sizes were calculated using SAS v9.3 (SAS Institute Inc., Cary, NC, USA). Given the preferred study power of 90% for non-inferiority trials and a clinical evaluability rate of 80%, it is estimated that a minimum sample size of 207 in each treatment arm is required (*n* = 414).

The non-inferiority margin was based on a combination of statistical reasoning and clinical judgement. The non-inferiority margin of 12.5% was considered clinically acceptable based on best current evidence [3]. Additionally, the Infectious Diseases Society of America has recommended a non-inferiority margin of between 10 and 15% for RCTs of antibiotic treatment for cellulitis [4]. Furthermore, current RCT evidence indicates that the efficacy of the comparator intervention (i.e. dual therapy with flucloxacillin and phenoxymethylpenicillin) is 83–87% efficacious. Our sample size for each trial arm was calculated based on an assumed treatment success rate of 85%, which is the midpoint of this 83–87% success range.

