### Analyses sets/populations/subgroups

For the analysis of the primary outcome both intention-to-treat (ITT) and per-protocol (PP) analyses will be performed. Initially, ITT analyses will be performed and will include all patients randomised to the trial regardless of whether they have taken the study drug or not. PP analysis will be defined as in a previous randomised controlled trial for uncomplicated skin abscesses conducted by Talan et al. in the United States [8]. It will include participants who either took ≥ 75% of the total doses of study drug or placebo during the first 5 days and had an in-person test-of-cure visit or were determined to have had clinical failure before the test-of-cure visit and received ≥ 75% of the doses provided during the first 48 h of the treatment period. In a non-inferiority trial setting it is suggested that a PP analysis may be more appropriate than ITT since it is more likely to reflect actual differences between the two treatments [9]. Furthermore, ITT analysis may be interpreted as being too liberal in a non-inferiority trial and may bias toward making the two treatments appear similar. As a result, both an ITT and PP analysis will be performed on the resulting data to assess non-inferiority. Non-inferiority will only be declared if both ITT and PP analysis support non-inferiority.

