### Primary endpoint

Non-inferiority of the primary outcome measure, the percentage of patients cured on day 14–21, will be assessed by calculating a two-sided 95% confidence interval (CI) on the difference of proportions between the two trial arms. Only one side of the confidence interval is of interest; this equates to a one-sided test with alpha at 0.05/2 (i.e. 0.025). If the upper limit of the CI is less than the non-inferiority margin threshold of 12.5%, then non-inferiority will be inferred.

Secondary analyses will investigate the effects of further adjustment for any variables displaying marked imbalance between the arms at baseline.

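### At the plan's own inputs, 90% power with 80% evaluability needs 215 patients per arm, not the stated minimum of 207; power in the evaluable set is about 89%

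*Protocol article*

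**What the plan says.** All the inputs are in the protocol article.

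- **Success rate.** The section on determination of sample size uses "an assumed treatment success rate of 85% with orally administered flucloxacillin and phenoxymethylpenicillin". It later gives the same rate for each arm ("Our sample size for each trial arm was calculated based on an assumed treatment success rate of 85" per cent), which I read as no true difference.
- **Margin and alpha.** The same section sets "a non-inferiority threshold *Δ* = 12.5% and *α* = 0.025 (as this is a non-inferiority study"). The primary endpoint section uses a two-sided 95% confidence interval and confirms the sidedness: "this equates to a one-sided test with alpha at 0.05/2 (i.e. 0.025").
- **Power.** "Given the preferred study power of 90% for non-inferiority trials".
- **Evaluability and result.** "a clinical evaluability rate of 80%, it is estimated that a minimum sample size of 207 in each treatment arm is required", 414 in total.
- **Decision rule.** The section on analysis sets adds: "Non-inferiority will only be declared if both ITT and PP analysis support non-inferiority".

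The article names the software (SAS v9.3). It shows neither the evaluable number before inflation nor the inflation step.

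**The concern.** The article presents 207 per arm as the minimum that delivers 90% power when one patient in five is not evaluable. That can be checked from the stated inputs, and it does not come out. To end with n evaluable patients when a fraction 0.8 is evaluable, one must randomise n/0.8. Adding 20% to n gives too few, because 80% of 1.2n is only 0.96n.

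At stake is whether the headline sample size and the headline power agree. If non-inferiority is not shown, readers will judge that result against a planned power of 90%, so the figure should follow from the assumptions printed beside it. The reduced set matters because a larger ITT set cannot make up for it: both analyses must succeed.

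**Working it through.** **Inputs** (all from the article): success p = 0.85 in both arms; margin Δ = 0.125; one-sided alpha 0.025, so z = 1.960; power 90%, so z = 1.282; evaluability 0.80; equal arms.

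**Step 1. Evaluable patients per arm** (normal approximation, unpooled variance):

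n = (1.960 + 1.282)² × 2 × 0.85 × 0.15 / 0.125² = 171.5, rounded up to **172**. Power at 172 per arm is 90.1%.

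**Step 2. Allow for 80% evaluability:** 172 / 0.80 = **215** per arm, 430 in total.

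**Step 3. Try to reproduce 207.** Multiplying instead of dividing gives 172 × 1.2 = 206.4, which rounds up to 207 exactly. Other routes miss it:

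| Variant | Evaluable per arm | After dividing by 0.8 |
|---|---|---|
| Unpooled variance | 172 | 215 |
| Farrington-Manning score | 179 | 224 |
| Continuity-corrected | 188 | 235 |
| Variance taken at 85% vs 72.5% | 220 | already above 207 |
| One-sided alpha 0.05 (not the stated alpha) | 140 | 175 |

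At the stated alpha, every variant tried needs at least 215. For 207 to supply 172 evaluable patients, evaluability would have to be 172/207 = 83.1%.

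**Step 4. Power that 207 gives in the evaluable set:** 207 × 0.80 = 165.6 per arm.

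Power = Φ(0.125 / √(0.255/165.6) − 1.960) = Φ(1.225) = **89.0%**.

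The exact binomial power of the Wald interval is 88.9% at 165 and 89.3% at 166 per arm. Simulation with each patient evaluable at random with probability 0.8 gives 89.0% for 207 randomised and 90.1% for 215. A Farrington-Manning score test at 165.6 per arm gives 87.6%.

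**Step 5. The joint rule, as a separate matter.** If all 207 per arm had an outcome at 85% success, ITT power alone would be about 94.5%. I simulated 207 per arm with random 80% evaluability, Wald intervals and the evaluable set standing in for the per-protocol set. ITT and evaluable-set success together then have about 88% probability if non-evaluable patients also cure at 85%. The article gives no cure rate for non-evaluable patients, so this figure rests on an assumption.

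**The case against.** **The loss is trivial.** The gap is 8 patients per arm, or 8/215 = 3.7%, and it costs about one point of power. The 80% is itself a planning assumption, and 83.1% would make 207 sufficient. The margin, alpha, primary analysis and decision rule are untouched. All of this stands, and it is why the point is minor. It does not make the sentence correct: the article calls 207 the minimum at 80%, and nothing elsewhere in it changes that.

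**The cause is not documented.** This also stands. A reader might conclude that the authors demonstrably multiplied by 1.2. The exact match makes that likely, but neither the 172 nor the inflation step is printed. The error in the result does not depend on how it arose.

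**The ITT-and-per-protocol rule makes the shortfall much larger.** A reader might infer this, but it merges two matters. The article does not claim 90% power for the joint rule, and the joint rule would cost power at 215 per arm too: my simulation gives about 89% there, with non-evaluable patients curing at 85%. Figures below about 88% at 207 need lower cure rates among non-evaluable patients, and no such rate is in the article. They also depend on how evaluability is modelled. At an assumed 30% cure rate, joint power is about 83% if exactly 166 per arm are evaluable in every trial, but about 79% if evaluability varies at random. No such range can be stated as a property of the design.

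**Evaluable is not the same as per-protocol.** This is fair. The article defines the per-protocol set by doses taken and an in-person test-of-cure visit, or by early failure with sufficient dosing. It gives no expected per-protocol rate. The 89% should therefore be described as power in the evaluable set.

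**Conclusion.** The stated minimum is wrong as written. At the article's own inputs it should be 215 per arm (430 in total), not 207 (414). With 207, power in the evaluable set is about 89.0% instead of 90%. This is a minor arithmetic error.

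The result rests on equal 85% success in the two arms, the unpooled normal approximation and exactly the stated 80% evaluability. The score and continuity-corrected versions need more patients, so the choice of method does not rescue 207.

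The documents do not support reading this as a seriously underpowered trial. The joint requirement lowers power somewhat further, but that is a feature of the decision rule and not a result of the inflation step, and its size depends on a cure rate that the article does not give.

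**What to change.** Replace the concluding figure in the sample-size section with wording to this effect:

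*172 evaluable patients per arm are needed for 90% power, which at 80% evaluability is 215 per arm (430 in total). With 207 per arm (about 166 evaluable) the power in the evaluable set is about 89%.*

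The paragraph may add that this power refers to a single analysis, and that power is somewhat lower when ITT and per-protocol must both succeed: about 88% if non-evaluable patients also cure at 85%, and less if they cure less often. Any such figure should carry its assumed cure rate.

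The cost is one corrected paragraph and a slightly less favourable power figure. No extra enrolment is needed, and no analysis, margin or decision rule changes.

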### Outcome measures/endpoints

#### Primary outcome measure

The primary outcome measure is investigator-determined clinical response measured at the TOC visit. Measurement of this outcome will be as follows:A suitably trained member of the study team will determine clinical cure at the TOC visit. This is a clinically determined response to treatment based on the judgement of a suitably trained member of the study teamDefinition of clinical cure:No treatment failure at any previous visitResolution or minimal presence of the following signs and symptoms from the baseline assessment based on the study investigator’s clinical assessment:ErythemaSwellingTendernessInduration

Follow-up assessments will be in person. In the unlikely event that this is not possible, the research nurse will contact the patient by telephone and obtain as much follow-up information from the patient as possible.

#### Secondary outcome measures

The principal secondary outcome measure is a ≥ 20% reduction in lesion surface area on day 2–3 after enrolment compared to the baseline visit. In addition, the following secondary outcome measures will be assessed:Clinical treatment failure at each follow-up visitAdherence and persistence of trial patients with outpatient antibiotic therapy at EOT (day 8–10 post enrolment)HRQoL assessments at each follow-up visitA pharmacoeconomic assessment of cost per QALY

##### 1. ECR measured on day 2–3

ECR measured on day 2–3 is defined as ≥ 20% reduction in the lesion surface area from that which was measured at enrolment. Objective measurement of lesion size is the US FDA-recommended outcome measure of choice. In order to enhance the validity of the study findings, an objective measure of the percentage decrease in the diameter of infection at day 2–3 will be utilized as a secondary outcome measure. Surface area measurement will be achieved by multiplying the vertical and horizontal diameter of the area of lesion.

##### 2. Clinical treatment failure

Any patient outcome designated as a clinical treatment failure at any time before and including the TOC visit will be categorised as a treatment failure.

##### 3. Adherence and persistence of trial patients with outpatient antibiotic therapy

Medication adherence will be measured at EOT in various ways:By self-reportHave you taken all of your antibiotic doses as prescribed? (yes/no)If not, how many times would you estimate you did not take your doses as prescribed?Did you finish your antibiotic course?If not, when did you stop? (day 0–7)
By counting the number of unused study medications at the EOT visit. Patients will be asked to bring their medication with them to the EOT visit so that a pill count can also be performedBy using an electronic monitoring system (MEMS® cap). The MEMS**®** cap will be used to measure adherence in a subset of 100 patients assigned to either treatment arm at the Beaumont Hospital study site only. The MEMS® cap will be fitted to the dispensed medication bottle. Patients will be informed that the cap will monitor each opening of the bottle and, as such, they should only open the bottle when they are about to ingest a dose. Any other openings should be recorded and the research team should be informed. The MEMS® cap should be returned with the clinical trials supplies on the follow-up visits

Medication persistence may be defined as the duration of time from initiation to discontinuation of therapy [5]. Persistence will be measured using the MEMS® cap in the subgroup of 100 patients. It will be measured by determining from the MEMS® cap report the time (in days) from the start day of treatment to the day of the last dose taken without regard for any missing doses or days in between. Missing doses and days will be described separately in descriptions of adherence.

